**Methods:**

In a four-arm, parallel, single-blind, randomized controlled trial (RCT), we will randomize 128 individuals with depression and 128 matched controls without depression to one of four study conditions: (1) a cognitive reappraisal training (CR); (2) CR enhanced with instructions to display anti-depressive facial expressions (CR + AFE); (3) facial muscle training focusing on anti-depressive facial expressions (AFE); and (4) a sham control condition. One week after diagnostic assessment, a single intervention of 90–120-minute duration will be administered, with a subsequent follow-up two weeks later. Depressed mood will serve as primary outcome. Secondary outcomes will include current positive mood, symptoms of depression, current suicidality, dysfunctional attitudes, automatic thoughts, emotional state, kinesthesia (i.e., facial expression, facial muscle activity, body posture), psychophysiological measures (e.g., heart rate (variability), respiration rate (variability), verbal acoustics), as well as feasibility measures (i.e., treatment integrity, compliance, usability, acceptability). Outcomes will be analyzed with multiple methods, such as hierarchical and conventional linear models and machine learning.

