**Further psychophysiological measures**							
Facial muscle activity^c^	Biopac MP160				X		
Respiration rate (variability)	Biopac MP160				X		
Heart rate (variability)	Biopac MP160				X		
	24 GHz & 61 GHz CW Radar systems (self-developed)				X		
Verbal acoustics	Microphone		X		X		
**Technical app data (e.g.**,** reaction time**,** item choice**,** credibility of emotion display)**	EmpkinS EKSpression app				X		

Note. T0 = Screening; T1 = diagnostic session one week before the training; T2 = assessment directly before the training; T3 = assessment directly after training completion; T4 = assessment two weeks after training completion. SCID-5-CV = Structured Clinical Interview for DSM-5 Disorders Clinician version; GRID-HAMD = GRID Hamilton Rating Scale for Depression; PHQ-8/-9 = Patient Health Questionnaire-8/-9; CES-D = Centre for Epidemiological Studies Depression Scale; DAS-A = Dysfunctional Attitude Scale version A; ATQ-R = Automatic Thoughts Questionnaire-Revised; ERSQ-ES A = part A of the Self-Report Instrument for the Assessment of Emotion-Specific Regulation Skills; UEQ-S = User Experience Questionnaire, short version

^a^Measures are taken continuously during the training. ^b^The main purpose of the video recordings during T1 was to determine inter-rater reliability of the diagnostic interviews. ^c^We will use a bipolar electromyogram to measure activity of the musculus corrugator supercilii, musculus zygomaticus major, musculus masseter (only in the AFE condition), and musculus orbicularis oculi

The training session will take place one week after the diagnostic session at the laboratory, taking approximately three hours in total. At the beginning, participants will be randomly allocated to study conditions. We will use numbered, sealed envelopes containing the respective allocation information. The envelopes will be prepared by a student assistant not otherwise involved in the study. Following a pre-assessment (T2) on a computer tablet via Unipark.com and the setup of the kinesthetic and physiological data acquisition (see below for details), participants will receive brief psychoeducational instructions about the interconnection of cognitions (thoughts), the body (e.g., facial expression) and emotion/mood. Then, they will complete the 90-120-minute intervention on a study smartphone. The training session will be concluded with a brief self-report post-assessment (T3).

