### Smartphone-based intervention

In all conditions, the training will consist of five distinct phases in total (see Fig. 2): As an initial step, a preparatory phase will serve as a baseline and resting period for physiological measures. Then, a mood induction phase will be initiated to induce a depressed mood prior to the first training phase. After the first training phase, a second mood induction and a second training phase will follow. Preparatory phase and both mood induction phases will be identical for all participants. The two training phases will differ depending on the condition that each participant has been allocated to.

During the preparatory phase, different stimuli will be presented to the participant via smartphone. These will alternate between live self-recordings of the participant and verbal stimuli: “hopeless” and “happy” as words congruent or incongruent with depressiveness, respectively, and “me,” “the world,” and “the future” corresponding with Beck’s cognitive triad of depression [42]. Each stimulus will be presented for five seconds in randomized order following the display of a fixation cross (3 s.) and will be shown twice, adding up to a total of twelve stimulus presentations. Before the first and after each stimulus presentation, two one-item self-reports of the current level of depressed and positive mood, respectively, will be collected.

The subsequent mood induction will follow a validated procedure [43, 44] and consist of ten depressogenic cognitions shown on-screen (e.g., “*My future is absolutely hopeless*”), which the participant will read aloud while listening to music inducing depressed mood (i.e., excerpt from “Adagio in G minor” by Tomaso Giovanni Albinoni). After the mood induction, participants will again rate their current level of depressed and positive mood.

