**Fig. 3 Fig3:**
[figure not shown]
Trial flow of the four study conditions. CR = cognitive reappraisal training; CR + AFE = cognitive reappraisal training enhanced by instructions to deliberately display anti-depressive facial expressions; AFE = facial muscle training focusing on anti-depressive facial expressions

*CR*. To work with the cognitions, participants are instructed to respond to each of them in three steps. First, the screen will display three statements expressing *rejection* of the depressogenic cognition or *approval* of the anti-depressive cognition. Second, three statements *affirming* the rejection/approval, and third, three *self-supporting* statements will be presented on the screen. In each step, participants will choose the subjectively most fitting statement by selecting it on the screen and reading it aloud. To conclude the trial, participants again read aloud the affirming and self-supporting statement (depressogenic cognition training) or all three positive statements (anti-depressive cognition training) they have selected in a combined fashion.

*CR + AFE.* In the CR + AFE condition, participants will follow the same three steps as in the CR condition, except that they are instructed to mirror them with congruent kinesthesia including mime, posture, and gesture. Step 1 will be accompanied by rejection/approval, Step 2 by approval/confidence, and Step 3 by joy (trials 1 to 10) or pride (trials 11 to 20).

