*AFE*. In the AFE condition, participants are instructed to first experience the elicited emotion, and then counteract depressogenic cognitions/strengthen anti-depressive cognitions by tensing or relaxing relevant facial muscles, for example, the forehead (i.e., the area between the eyebrows). In total, four different facial muscles are targeted in this condition: (1) m. corrugator supercilii or the “frowning muscle,” (2) m. zygomaticus, the muscle relevant to lifting the corners of the mouth to smile, (3) m. orbicularis oculi, a circular muscle around the eye activated when smiling, and (4) m. masseter or the “chewing muscle,” used when clenching one’s teeth, as well as different combinations of all four facial muscles. The exact number of combinations and repetitions can be found in Supplementary Table 1. When participants perform the respective expression, the study therapist commands the app to zoom-out depressogenic and zoom-in anti-depressive statements on the smartphone screen according to the intensity of participant’s performance as trainer-operated biofeedback.

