#### Kinesthesia measures

For the analysis of (affective) facial expression, videos will be recorded using the built-in smartphone camera, which will be positioned in front of the participant at a distance of approximately 40 cm. A video for each emotion induction and training trial will be recorded, adding up to a total of 44 videos. In addition to these smartphone videos, two high-resolution RGB cameras (Sony SRG-300 H) will be used, one of them positioned directly in front of and the other to one side of the participant, both approximately 1.2 m away. Together, the cameras will record the participant’s face and upper body. We will extract information on facial expression (i.e., facial action units, eye gaze, head position, and facial emotions) from recordings of the front camera and information on body posture from the side camera. A third RGB camera will focus on the study therapist during the diagnostic session and training for adherence checks. Additionally, we will use an Azure Kinect depth camera (Microsoft, Redmond, WA, USA) to estimate participants’ body posture using the Azure Body Tracking SDK.

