#### Efficacy of the reappraisal training augmented with facial expressions

In order to study the effectiveness of the EmpkinS-EKSpression app-based interventions, generalized linear models (GLMs) of the between-subject factors “diagnostic group” (with depression vs. without depression) and “intervention condition” (CR vs. CR + AFE vs. AFE vs. sham control), as well as the within-subject factor “time of assessment” will be applied in a stepwise fashion.

Regarding the primary outcome of depressed mood, we will first examine whether the mood induction phase *induces* depressed mood using a paired *t*-test with the pre- and post-mood-ratings as dependent variable (manipulation check). Further, hierarchical linear models (HLMs) will be implemented to assess whether the EmpkinS-EKSpression app-based interventions are effective in *reducing* depressed mood. As a first step, we will compare the CR condition with the sham control condition and the CR + AFE with the CR condition to study whether cognitive reappraisal training can be augmented with anti-depressive kinesthesia. As a second step, we will compare the AFE condition with the sham control condition. For continuously assessed secondary outcomes (i.e., positive mood, app data), corresponding analyses will be conducted.

With regard to secondary outcomes (i.e., GRID-HAMD, CES-D, current suicidality, ERSQ-ES, DAS-A, ATQ-R) assessed at pre-treatment, post-treatment, and/or follow-up, as well as pre/post mood-ratings, we will implement mixed analyses of variance (ANOVAs), again with the between-subject-factor, “study condition” (CR, CR + AFE, AFE, sham control) and the within-subject factor, “time.” Feasibility measures (treatment integrity, compliance, usability, acceptability) will be descriptively analyzed and contrasted between study conditions utilizing one-way ANOVAs. Finally, changes in kinesthesia and other psychophysiological measures over the course of the intervention, as well as differences between diagnostic groups and intervention conditions will be examined using, again, HLMs. All analyses will be conducted using the whole sample, as well as with the added between-subject-factor, “diagnostic group” (with vs. without depression). All analyses will be conducted with a significance level of α = 0.05. One-tailed tests will be used when the algebraic sign of the test statistic is specified; otherwise, two-tailed tests will be used.

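### Face and posture during training trials are compared between conditions as outcomes although some arms are instructed to change them; there, CR + AFE vs CR and AFE vs sham show adherence, not a training effect

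*Protocol article*

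**What the plan says.** The abstract (Methods) includes among the secondary outcomes "kinesthesia (i.e., facial expression, facial muscle activity, body posture), psychophysiological measures (e.g., heart rate (variability), respiration rate (variability), verbal acoustics". Table 1 schedules these signals for the training session, with the footnote "Measures are taken continuously during the training". RGB video and microphone are also used at T1, before randomisation. None of these signals is scheduled at T3 or T4.

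The Statistical analysis plan, subsection Efficacy of the reappraisal training augmented with facial expressions, uses hierarchical linear models to examine "changes in kinesthesia and other psychophysiological measures over the course of the intervention, as well as differences between diagnostic groups and intervention conditions". The same subsection labels the test of the mood induction a manipulation check. It gives the kinesthesia comparison no such label and does not limit it to particular periods.

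Under Training for the three intervention conditions, CR + AFE participants go through the CR steps, "except that they are instructed to mirror them with congruent kinesthesia including mime, posture, and gesture". AFE participants work on the cognitions "by tensing or relaxing relevant facial muscles"; the targets are corrugator, zygomaticus, orbicularis oculi and masseter. Further psychophysiological measures takes EMG from the same four muscles: the masseter in AFE only, and EMG as a whole in all AFE participants but a random half of the other arms. CR participants select statements and read them aloud; sham participants sort shapes. The text gives neither arm a face or posture instruction.

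Two further statements matter. Smartphone-based intervention says: "Preparatory phase and both mood induction phases will be identical for all participants". Kinesthesia measures says: "A video for each emotion induction and training trial will be recorded".

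**The concern.** A measure that one arm is told to change, and the comparator is not, cannot show an effect of treatment while the instruction is in force. If CR + AFE participants smile more than CR participants during trials in which only the former are asked to display joy, the difference shows compliance. The same holds for corrugator activity in AFE vs sham.

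CR + AFE vs CR is also the contrast that the plan uses for its main scientific question, whether facial expression augments reappraisal. A significant kinesthesia result on that contrast, reported under an efficacy heading, could be taken as evidence that training changes depressive expression. The question of interest is whether expression differs once nobody is instructed to alter it, and the trial already records a period in which that can be asked.

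**Working it through.** **1. How much of the recording is condition-specific.** Inputs are from Training for the three intervention conditions (20 trials in each of two phases) and Smartphone-based intervention (two mood inductions).

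- Training trials: 2 × 20 = 40.
- Inductions plus trials: 2 + 40 = 42. Kinesthesia measures states 44 videos; the article does not explain the other two.
- Share that is training trials: 40/42 = 95%, or 40/44 = 91%.

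This counts smartphone clips only. It leaves out the preparatory phase (twelve stimulus presentations, also the same in all arms) and does not measure time in the continuous signals, so it is descriptive.

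**2. Which contrasts are fixed by instruction during training trials.** The rows are the three contrasts that the plan names for depressed mood.

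| Contrast | Face and facial EMG | Posture | Voice |
|---|---|---|---|
| CR + AFE vs CR | Fixed by instruction | Fixed by instruction | Same spoken steps, no voice instruction |
| AFE vs sham | Fixed by instruction | No instruction in either arm | Depends on whether sham speaks |
| CR vs sham | No instruction; indirect at most, through speaking | No instruction in either arm | Depends on whether sham speaks |

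Three of the nine cells are fixed by instruction. Two more depend on the sham trial flow, one is touched only indirectly, and three are free of the problem. The masseter is recorded only in AFE, so it cannot be compared between conditions. Therapist-rated credibility of the emotional display, part of the app data, is rated only in CR and CR + AFE, so it has no sham contrast. In CR + AFE vs CR it meets the same objection as face and posture.

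**3. How readily an instruction-only difference becomes significant.** The plan's sample size supplies the arm size. For d = 0.5, two-sided α = 0.05 and power 0.80, the normal approximation 2(1.960 + 0.842)²/0.5² gives 62.8, so 63 per arm. The t-test version gives 63.8, so 64 = 2 × 32 per condition, and 4 × 64 = 256 as stated. Power at 64 per arm is 0.801.

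Now assume that training has no effect on expression and that the instruction shifts the measure by s SD. The shifts are assumptions; the article gives none. With one value per participant and 64 per arm, the noncentrality is s√(64/2) = 5.66s.

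| Assumed shift s | Noncentrality | Probability of significance |
|---|---|---|
| 0.25 | 1.41 | 0.29 |
| 0.5 | 2.83 | 0.80 |
| 1.0 | 5.66 | about 1.00 |

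For EMG, half of 64 is 32 in CR, CR + AFE and sham. At s = 0.5 the probability is 0.50 for CR + AFE vs CR (32 vs 32) and 0.63 for AFE vs sham (64 vs 32).

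**4. Which recordings share one task across arms.** The preparatory phase and the first induction precede all training. The second induction follows training phase 1 and precedes phase 2. It is therefore the only period that is both identical in all arms and after some training. It is on video, and everyone reads aloud in it, sham included. No such period follows phase 2, because T3 is a self-report and T4 a telephone interview with online questionnaires.

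**The case against.** The case for leaving the text alone has four parts.

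- **Outcome status.** Only the abstract calls kinesthesia a secondary outcome, in a list that also includes feasibility measures. Table 1, the Measures section and the analysis section's own lists of secondary outcomes set it apart. This stands and softens the point, but the comparison remains planned under the efficacy heading.
- **No efficacy claim.** The wording about reducing something attaches to depressed mood, and the Discussion ties benefit to mood. This also stands. A reader might infer that the investigators intend to claim efficacy from kinesthesia; the article does not say so.
- **Window left open.** The course of the intervention includes the common phases, and details of windows may sit in an analysis plan that is not shown. This stands in part. The text does not force pooling of all segments, but as written it takes in the instructed trials without separating them.
- **The replacement has weaknesses.** The inductions are not neutral, since participants read depressogenic statements to sad music. What half the participants have trained by then differs from the other half, because phase order is counterbalanced. Both are true and are costs of the fix.

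Two stronger readings are tempting and not supported. The first is that every between-condition difference in kinesthesia or physiology merely reflects instruction. The table above contradicts this, and no arm receives a breathing instruction. The second is that sham participants are silent, so that voice comparisons fail. That rests on the short description of the sham task. The section on the primary outcome places a rating in each trial after a statement is read aloud, with no exception for sham, and Fig. 3, which gives the sham trial flow, is not shown.

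**Conclusion.** The concern holds for a defined set of comparisons. During training trials, CR + AFE vs CR on facial expression, facial EMG and posture, and AFE vs sham on facial expression and facial EMG, measure adherence. Posture in CR vs sham and in AFE vs sham, and voice in CR + AFE vs CR, are not affected in this way. Nor is the diagnostic-group comparison, provided condition is balanced or adjusted for. Any voice problem with sham is conditional on its trial flow.

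The conclusion rests on the instructions as printed and needs no numerical assumption. Only the illustration of size does: an instruction-only shift between 0.25 and 1.0 SD would be significant with probability 0.29 to about 1.00 at 64 per arm. No figure in the article is disputed and the primary outcome is unaffected. The change is worth making because it is cheap and prevents a misreading on the trial's key contrast.

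**What to change.** **Relabel.** State that face, posture, facial EMG and therapist-rated credibility in the training trials are a manipulation or adherence check wherever the compared arms have different instructions.

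**Redefine the comparison.** Base the between-condition kinesthesia comparison on the second mood induction, adjusted for the same measure in the first induction and for training-phase order. As described, sham has no depressogenic or anti-depressive order. In contrasts with sham the order term should therefore be centred within the intervention arm, so that the contrast averages over the two orders.

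**Cost.** Wording only, with no new recording. The outcome then rests on one short window reflecting training phase 1 alone, with depressogenic or anti-depressive content according to the order. EMG is available for only half of CR, CR + AFE and sham, so power there is lower (0.50 to 0.63 for a 0.5 SD difference, before any gain from baseline adjustment). The masseter must be left out of the comparison.

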### Participants

We will recruit two participant groups of equal size with differing diagnostic status: one group of individuals with clinically relevant depressive symptomatology and a control group of individuals without depression. The diagnostic groups will be matched according to gender and age. For the depression group, the main inclusion criterion is the presence of a diagnosis from the depressive spectrum according to ICD-10 criteria (F32 ‘depressive episode’, F33 ‘recurrent depressive disorder’, F34.1 ‘dysthymia’, and F43.20 & F43.21 ‘adjustment disorder with depressive symptoms’ [38]) according to the Structured Clinical Interview for DSM-5 Disorders - Clinician version (SCID-5-CV; German Version: [39]). The main inclusion criterion for the group without depression is a score < 10 on the Patient Health Questionnaire (PHQ)-8 [40]. Additional inclusion criteria for both groups include being ≥ 18 years, being able and willing to provide informed consent regarding study participation, and having sufficient German language skills (at least level B2 according to the Common European Framework of Reference for Languages). Exclusion criteria included the presence of any psychotic disorder (ICD-10 F2x), any substance dependence disorder other than nicotine (ICD-10 F1x.2), acute suicidality, any impairment of facial expression (e.g., due to facial paralysis or recent Botox treatment or autism spectrum disorder), and any type of dyschromatopsia. To ensure maximum external validity, we refrain from applying further potential exclusion criteria such as other clinical comorbidities, or concurrent pharmaco- or psychotherapy, but will record this information.

A power analysis was conducted with G*Power [41] to determine the necessary sample size for a 2-group-comparison of each of the intervention conditions (CR, CR + AFE, AFE) with the sham control condition. In absence of similar studies serving as reference for the determination of a critical effect, a team of three clinical experts agreed that an effect size of *d* = 0.5 would be therapeutically relevant. The power analysis yielded a necessary sample size of *n* = 32 for each of the four intervention conditions and two diagnostic groups based on a 2-sided analysis, a critical alpha-level of α = 0.05, and a power of β = 0.80. Hence, we will include *N* = 256 participants in total, composed in equal parts of participants with depression (*n* = 128) and without depression (*n* = 128).

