#### Preprocessing of kinesthesia and further psychophysiological data

Video data will be primarily processed with the FaceReader software [62], which offers an extensive array of visual features, including probabilities associated with basic emotions such as neutral, happy, sad, angry, surprised, scared, disgusted, and contempt - all discernible within each video frame. Additionally, it provides measurements of valence and arousal that are essential for understanding emotional states. Furthermore, it allows the extraction of so-called Facial Action Units (e.g., “Eyes Closed”, “Lip Stretcher”), offering insights into the intensity of expressions ranging between 0 and 1, and estimates head position and orientation in 3D (e.g., pitch, yaw, and roll rotation angles), complemented by 2D and 3D facial landmarks. The Facial Action Units and their variations provide detailed information on facial expressions and movements [63]. With regard to videos recorded with the Azure Kinect depth camera, we will extract depth information of body posture (i.e., the distance of each body part from the camera). Psychophysiological data, i.e., EMG, ECG, and respiration signals, will be preprocessed by extracting generic as well as specific features using various methods, particularly focusing on bio-signal feature extraction. Generic features of all psychophysiological data include mean, standard deviation, minimum, and maximum. Specific features of EMG signals include mean absolute value (MAV) and root mean square (RMS), specific features of ECG signals include heart rate and RR intervals, and specific features of respiration signals include respiration rate and respiration rate variability.

Cross-sectional comparisons between diagnostic groups (i.e., with vs. without depression) regarding baseline demographic, health-related, and clinical characteristics will be conducted using *t*-tests for continuous and Χ^2^-contingency tables for dichotomous variables, respectively.

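### The diagnostic groups are matched on gender and age, but the described comparisons between them do not use the matching factors, so tests of overall level differences are conservative wherever age or gender predicts the measure

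*Protocol article*

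**What the plan says.** Matching is part of the design. The Participants section states: "The diagnostic groups will be matched according to gender and age". The Abstract (Methods) says the same: "we will randomize 128 individuals with depression and 128 matched controls without depression". Neither place says whether matching is one-to-one or by frequency.

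The analysis of diagnostic group is described in two places.

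- Preprocessing of kinesthesia and further psychophysiological data, last paragraph: "Cross-sectional comparisons between diagnostic groups (i.e., with vs. without depression) regarding baseline demographic, health-related, and clinical characteristics will be conducted", with t-tests for continuous variables and chi-square tables for dichotomous ones. No paired or adjusted form is named.
- Efficacy of the reappraisal training augmented with facial expressions: the opening sentence lists diagnostic group, intervention condition and time of assessment as factors. Diagnostic group is later added as a between-subject factor to all analyses. For kinesthetic and psychophysiological measures, change over the session and "differences between diagnostic groups and intervention conditions will be examined using, again, HLMs".

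Age, gender and a matched-set effect appear in neither description. Both variables are collected (Demographic and health-related information, screening, and diagnostics).

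**The concern.** Matching on a variable that predicts the outcome makes the two group means positively correlated. The difference between the groups then varies less from sample to sample than it would with independently drawn groups. A test that treats the groups as independent, without the matching variables, leaves their variance in the error term. Its intervals are too wide and its p-values too large. The error goes in one direction only, towards missing a real difference.

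What is at stake is the second aim, stated at the end of the Background: how far single kinesthetic markers are associated with depression. The level contrasts between diagnostic groups serve that aim. Heart rate variability, respiration, voice and facial measures could plausibly depend on age or gender, but the article gives no figure for this.

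**Working it through.** **The plan's own figure.** The sample size is for a "2-group-comparison of each of the intervention conditions (CR, CR + AFE, AFE) with the sham control condition", "based on a 2-sided analysis, a critical alpha-level of α = 0.05, and a power of β = 0.80", with d = 0.5. A two-sample t-test on those inputs needs 63.8, so 64 per condition, and 4 × 64 = 256. The stated total is reproduced with both diagnostic groups pooled (32 + 32 per condition). This calculation concerns condition against sham. The article states no effect size or power for depressed against non-depressed.

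**Inputs for the check.** n = 128 per diagnostic group (Participants) and two-sided alpha 0.05. Two inputs are assumptions. Rho is the share of within-group variance explained by age and gender, which equals the within-pair correlation under exact one-to-one matching; it is varied from 0 to 0.30. The standardised level difference d is set at 0.30, 0.35 and 0.50. The value 0.35 has about 80% power without matching, and 0.50 is the article's figure for a different comparison.

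**Formulas** (outcome SD = 1)

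- Standard error used by the test: √(2/n) = √(2/128) = 0.125.
- Actual standard error under matching: √(2(1−ρ)/n).
- Ratio of the two: 1/√(1−ρ).
- Actual type I error of the unmatched test: 2[1 − Φ(1.96/√(1−ρ))].
- Power ignoring the matching: Φ((δ − 1.96)/√(1−ρ)), with δ = d√(n/2) = 8d.
- Power using the matching factors: two-sample t-test with effect d/√(1−ρ).

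Example with d = 0.30 and ρ = 0.30: δ = 2.40, (2.40 − 1.96)/0.837 = 0.526, so power ignoring the matching is 0.70. With the factors in the model the effect becomes 0.30/0.837 = 0.359 and power is 0.815.

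| ρ | SE ratio | Type I error | d = 0.30: ignoring / using | d = 0.35: ignoring / using | d = 0.50: ignoring / using |
|---|---|---|---|---|---|
| 0 | 1.000 | 0.050 | 0.67 / 0.67 | 0.80 / 0.80 | 0.979 / 0.979 |
| 0.10 | 1.054 | 0.039 | 0.679 / 0.712 | 0.812 / 0.837 | 0.984 / 0.987 |
| 0.25 | 1.155 | 0.024 | 0.694 / 0.788 | 0.834 / 0.896 | 0.991 / 0.996 |
| 0.30 | 1.195 | 0.019 | 0.701 / 0.815 | 0.842 / 0.915 | 0.993 / 0.997 |

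The loss at ρ = 0.10 is 2 to 3 points. At ρ = 0.25 it is about 6 points for d = 0.35 and 9 for d = 0.30. At ρ = 0.30 it is about 7 and 11 points. At d = 0.50 it is about half a point. Even against a wholly unmatched design (0.979), the d = 0.50 difference at ρ = 0.30 is only 1.8 points.

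**Simulation check.** 20,000 data sets of 128 matched pairs gave type I error of 0.050, 0.038 and 0.020 for the independent test at ρ = 0, 0.10 and 0.30, against about 0.05 for the paired test. At d = 0.30 and ρ = 0.30, power was 0.70 against 0.81.

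**EMG subsample.** EMG is taken in all AFE participants and half of the rest: 32 + 3 × 16 = 80 per diagnostic group. At d = 0.50 and ρ = 0.30, power using the factors is 0.964. Ignoring them it is about 0.92 if the age and gender balance carries over to the subsample, and 0.882 if it does not. The loss is therefore about 4 to 8 points.

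**The case against.** The strongest reply is that the point rests partly on silence. The sentence on kinesthetic measures lists no covariates or random effects, and a journal article commonly leaves these to the full analysis plan. A reader might infer that age and gender have been excluded. The text does not support that: they are unmentioned. What remains is that the factors the section does name omit them. At baseline, the section on efficacy writes paired when it means a paired t-test, so the plain t-tests there read as unpaired.

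A reader might also infer that every comparison between the groups is affected. That is too wide. The Automated detection of depression section judges classification by sensitivity, specificity and balanced accuracy, which do not rest on this standard error. In group-by-time contrasts, stable age and gender differences cancel within person, so the calculation applies to overall level differences.

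Two further replies stand. Matching still protects against confounding by age and gender when the analysis ignores it, so only precision is lost. And testing age and gender at baseline between non-randomised groups is a reporting choice rather than an error.

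One reply does not stand: that d = 0.5 bounds the loss. Clinical experts judged that value as one that "would be therapeutically relevant" for an intervention, and it says nothing about how large marker differences are.

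**Conclusion.** The point holds as a modest matter of precision. As described, the diagnostic-group comparisons do not use the matching factors. Tests of overall level differences are therefore conservative for any measure that age or gender predicts, and never anti-conservative.

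The size rests wholly on an assumed rho. There is no loss at 0, little at 0.10 or below, and a visible loss from about 0.25 if marker differences are around 0.30 to 0.35. At d = 0.5 with 128 per group the loss is negligible. It would be tempting to conclude that standard errors are too large and power is lost throughout, but the documents give no correlation that would support an unconditional statement.

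The randomised comparisons between conditions, including the primary outcome, do not compare the matched groups and are not affected by this point. It deserves a change because the remedy costs almost nothing and serves a stated aim, not because a main conclusion is at risk.

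**What to change.** In the section on efficacy, state that models estimating a diagnostic-group difference in kinesthetic and psychophysiological measures include age and gender as fixed covariates, and that the adjusted difference is the main estimate. This works whether matching was one-to-one or by frequency. It also works in the EMG subsample, where random selection may break pairs. In Participants, say which type of matching was used.

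The cost is wording and two degrees of freedom (age entered linearly, gender with two categories); no new data are needed. Replacing the baseline p-values for age and gender with descriptive differences is optional.
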